## Abstract

**Background:** Neurogenic lower urinary tract dysfunction (NLUTD) is common among people with multiple sclerosis (MS) with a pooled prevalence of 68.41% using self-report measures and 63.95% using urodynamic studies. Transcutaneous tibial nerve stimulation (TTNS) is a non-invasive option to manage bladder storage symptoms; however, the potential efficacy of TTNS among people with MS is based on a small number of studies with the absence of high-quality evidence relating to efficacy, and lack of clarity of the optimal electrical stimulation parameters and frequency, duration and number of treatment sessions. This study aims to assess whether TTNS is feasible and acceptable as a treatment for bladder storage symptoms in people with MS.

**Methods:** We will use a single-arm experimental study to explore the feasibility and acceptability of TTNS in the treatment of bladder storage symptoms in MS. The CONSORT extension for pilot and feasibility studies will be followed to standardise the conduct and reporting of the study. The recruitment plan is twofold: 1) Open recruitment for people with MS through MS Ireland’s communication channels; 2) recruitment from a convenience sample of people with MS who have previously participated in a qualitative interview study of urinary symptoms. We will assess recruitment/retention rates, the urinary symptoms changes and the effect on quality of life pre and post intervention using ICIQ-OAB, 3-day bladder diary, King’s Health Questionnaire and collect self-reported data on adherence and adverse events. Acceptability of using TTNS will be evaluated at the end of intervention. This study has been reviewed and approved by the Education and Health Science’s Faculty Research Ethics Committee, University of Limerick [2020_06_07_EHS].

**Conclusion: **It is anticipated that assessing the feasibility and acceptability of TTNS for storage bladder symptoms in MS will inform the development of a definitive randomised trial.

**Trial registration**: ClinicalTrials.gov
NCT04528784
****27/08/2020

## Background

Neurogenic lower urinary tract dysfunction is defined by the International Continence Society (ICS) as “lower urinary tract symptoms (LUTSs) in the presence of a relevant neurological disease” (
Gajewski *et al*., 2018). Storage symptoms associated with LUTS include frequency, urgency, nocturia, and/or incontinence; voiding symptoms resulting in hesitancy, slow stream, intermittency, dysuria, straining, terminal dripple, need to immediately re-void, splitting or spraying whereas post micturition symptoms include incomplete bladder emptying and/or post micturition dribble (
Gajewski *et al*., 2018). The range and severity of neurogenic bladder symptoms depend on the location of the neurologic lesions (
Li *et al*., 2016;
Peter & Peter, 2012), with more pronounced symptoms in people with MS associated with lesions at the pontine micturition centre (PMC) leading to storage symptoms and or the supra sacral lesions resulting in both storage and voiding symptoms accompanied with an increased post-void residual (
Haylen *et al*., 2010;
McCombe *et al*., 2009;
Panicker *et al*., 2015). 

We recently undertook a systematic review and meta- analysis which demonstrated that LUTSs are prevalent in people with MS with a pooled prevalence of 68.41% using self-report measures and 63.95% using urodynamic studies. When considering types of LUTSs, urinary frequency was the predominant symptom followed by urgency with a pooled prevalence estimate of 73.45% and 63.87% respectively using self-report measures. Detrusor overactivity was found to be the most prevalent urodynamic symptom, with a pooled prevalence estimate of 42.9% followed by detrusor sphincter dyssynergia at 35.44% (
[name] *et al*., 2020). The high prevalence of urinary symptoms among people with MS is concerning as several studies have highlighted the negative consequences of urinary symptoms for quality of life (
Browne *et al*., 2015;
Finlayson *et al*., 2006;
Nortvedt *et al*., 2001;
Vitkova *et al*., 2014). Studies have shown that urinary incontinence is considered as one of the worst morbidities associated with MS (
Fowler *et al*., 2009;
Nakipoglu *et al*., 2009). Urinary symptoms including loss of urine that results in fear of leaking in public is considered as a barrier to engaging in physical activities among people with MS (
Kayes *et al*., 2011). Furthermore, an increased risk of mortality and an aggravation of MS symptoms following an episode of urinary tract infection (UTIs) has been reported (
Abrams *et al*., 2017). Timely diagnosis and proper management are of utmost importance in maintaining good quality of life among people with MS and urinary symptoms.

Current therapeutic interventions for storage symptoms include pharmacologic therapy, behavioural interventions, pelvic floor muscle training (PFMT), and/ or neuromodulation. Pharmacologic interventions such as the use of anticholinergic medication are considered a first-line treatment for neurogenic bladder population (
Chapple *et al*., 2008;
Tornic & Panicker, 2018). Anticholinergic short-term efficacy has been reported in previous studies, however, limited long-term efficacy due to side effects and lack of tolerance was reported (
de Seze *et al*., 2011;
Fowler *et al*., 2009;
Li *et al*., 2016;
Panicker *et al*., 2015;
Stöhrer *et al*., 2009;
Tornic & Panicker, 2018;
Valles-Antuna *et al*., 2017). The reported side effects include; gastrointestinal tract disorders, central nervous system particularly worsening in cognition and deterioration in memory, dry mouth, impact on complete bladder emptying and increase cost.

A systematic review identified very few high quality studies of non-pharmacological interventions such as behavioural interventions including management of fluid intake, bladder retraining and scheduled voiding among a neurogenic population including people with MS (
Panicker *et al*., 2015). Combined pelvic floor muscle training (PFMT) therapy with electromyography (EMG) biofeedback and intravaginal neuromuscular electrical stimulation (NMES) reduced urinary symptoms including number of leaks and pad test among 30 females with MS when compared to PFMT alone or PFMT and EMG biofeedback (
McClurg *et al*., 2006). A recent systematic review showed that PFMT alone or in conjunction with other interventions among people with MS is also considered to be effective and classified as a first-line treatment approach (
Tornic & Panicker, 2018). Of concern, across numerous studies with non-neurological populations adherence to PFMT has been shown to be the main factor influencing the improvement of urinary symptoms (
Bø *et al*., 2005;
Prasad *et al*., 2019;
Sacomori *et al*., 2019). One study showed some barriers to adherence among postpartum women included forgetfulness, lack of time, and chores related to childcare (
Sacomori *et al*., 2019). On the other hand, another study showed that using simple reminder methods could improve the adherence rate of PFMT and consequently improve urinary symptoms (
Prasad *et al*., 2019). Further studies are needed to assess adherence to PFMT among people with MS and urinary symptoms and the influence of adherence on urinary symptoms in MS.

The European Association of Urology (EAU), American Urology Association (AUA), and UK National Institute for Care and Clinical Excellence (NICE) recommend combined therapeutic interventions of PFMT and behavioural intervention for non-neurogenic OAB symptoms (
Nambiar & Lucas, 2014) with no clear recommendations for neurogenic bladder symptoms. Intra-detrusor Onabotulinum toxin A (BoNT-A) injection is the most effective therapeutic intervention that classified as a second-line intervention for neurogenic bladder according to EAU guidelines (
Nambiar & Lucas, 2014;
Tornic & Panicker, 2018). Despite the reported efficacy of this intervention among neurogenic population and particularly people with MS in improving subjective urinary symptoms and urodynamic parameters (
Cruz *et al*., 2011;
Denys *et al*., 2017;
Fowler *et al*., 2009;
Kalsi *et al*., 2007;
McCombe *et al*., 2009;
Woodwar, 2004), several adverse events and limitations have been reported including; generalised muscle weakness, the need for repeated injections, increased risk of urinary tract infections (UTIs), increased risk of post-void residual (PVR) due to decline in bladder contractility resulting in the need of clean intermittent catheterization (CIC) afterwards, and rare but severe side effects were also reported such as respiratory problems (
Fowler *et al*., 2009;
Groen *et al*., 2016;
Kalsi *et al*., 2007;
Panicker & Fowler, 2015;
Stöhrer *et al*., 2009;
Tornic & Panicker, 2018). Although the literature reported the required dosage for BoNT-A injection is 100 unit (
Mehnert *et al*., 2010), the needed dosage for each treatment session is still debatable (
Sahai *et al*., 2010).

Neuromodulation is another available intervention for neurogenic storage symptoms among people with MS. This intervention may include non-invasive, semi-invasive or an invasive surgical procedure. Non-invasive neuromodulation techniques include electrical stimulation of peripheral nerves such as pudendal nerve, dorsal genital nerves, and/ or tibial nerve. Although some studies showed a significant improvement of urinary symptoms using pudendal nerve or dorsal genital nerves among non-neurogenic OAB population, there is a need for further large high quality studies (
Jaqua & Powell, 2017;
Janssen *et al*., 2017), with a lack of clear efficacy among neurogenic bladder populations.

Tibial nerve stimulation proximal to medial malleolus using adhesive cutaneous electrodes is another form of non-invasive neuromodulation for bladder storage management called transcutaneous tibial nerve stimulation (TTNS). Percutaneous Tibial Nerve Stimulation (PTNS) is a semi-invasive neuromodulation in which needle electrode is used to stimulate the tibial nerve fibres. Therefore, TTNS could be an alternative intervention among people with MS. Recent reviews have shown that tibial nerve stimulation may be effective in managing storage symptoms in people with non-neurogenic and neurogenic bladder with future high quality studies needed among people with MS (
Aharony *et al*., 2017;
Panicker *et al*., 2015;
Schneider *et al*., 2015;
Tornic & Panicker, 2018). The tibial nerve is a mixed nerve containing sensory and motor fibres of L4-S3, and it originates from the same segments of the spinal cord as the innervation to the bladder, pelvic floor, and rectum. The exact mechanism through which tibial nerve neuromodulation potentially treats bladder storage related symptoms is not yet fully understood (
Arya & Weissbart, 2017;
Gaziev *et al*., 2013;
Joussain & Denys, 2015;
Valles-Antuna *et al*., 2017). However, it is believed that stimulation of the tibial nerve with low-frequency pulses at tolerable intensity can produce inhibition of the spinothalamic neurons within the spinal cord, reduce firing input to the pontine micturition centres (PMC), which in turn inhibits the information facilitated by those nerves to the bladder (
Chancellor & Chartier-Kastler, 2000;
Choudhary *et al*., 2016;
de Groat, 1997;
Devane *et al*., 2015;
Zecca *et al*., 2016). Neuromodulation may also have supra-spinal effects which has been investigated in human studies by studying somatosensory evoked potentials before and after Percutaneous tibial nerve stimulation (PTNS) and sacral neuromodulation (SNM). The results showed alterations in somatosensory evoked potential (
Finazzi-Agrò *et al*., 2009;
Valles-Antuna *et al*., 2017). This means that stimulation at the tibial nerve, results in modifications of synaptic efficiency through the somatosensory pathway providing information on the function of somatosensory cortical structures at the spino-thalamic level. Although people with MS might have scattered lesions at spinal cord level, some studies showed some promising evidence from tibial nerve stimulation intervention for bladder control in MS. Further studies are needed to determine the correlation between spinal cord lesions and tibial nerve stimulation intervention among people with MS and bladder storage symptoms.

Our review of the literature revealed few studies investigating TTNS among neurogenic bladder (
Amarenco *et al*., 2003;
Monteiro *et al*., 2014;
Perissinotto *et al*., 2015;
Valles-Antuna *et al*., 2017). Specific to people with MS, two experimental studies were identified (
de Seze *et al*., 2011;
Seth *et al*., 2018). In the uncontrolled experimental study by
de Seze *et al*. (2011); the authors recruited 70 people with MS and OAB. All participants were asked to apply TTNS daily for 20 minutes for 12 weeks. This study found significant improvements in urinary related symptoms of urgency, frequency, and nocturia in 82.6% at the end of week 4, and 83.3% improvement at the end of week 12. Urodynamic studies showed significant improvement by increasing maximum cystometric capacity and reflex volume in about half of the participants (51.2%.).

 A second study was a randomised pilot study assessing the safety, acceptability and pilot efficacy of transcutaneous low-frequency TTNS using self-applicating ambulatory skin-adhering device stimulating the tibial nerve called
geko
^TM^ at a frequency of 1 Hz. The study compared two different protocol of TTNS 30 min daily vs. 30 min weekly, for 12 weeks between 24 MS participants with OAB to 24 participants with idiopathic OAB. TTNS was shown to be safe, acceptable and significant improvements in urinary symptoms including OAB were reported for both groups (
Seth *et al*., 2015;
Seth *et al*., 2018). The electrical stimulation parameters for both groups were at 27 mA current, with 1 Hz current frequency and pulse width was between 70 and 560 µs and was consecutively increased depending upon the maximum tolerable sensory and best sensory-motor response.

The potential efficacy of TTNS among people with MS with urinary symptoms is based on a small number of studies with a large number of authors identifying the absence of high-quality evidence relating to the electrical stimulation parameters, frequency of treatment per week, and total number of sessions (
Booth *et al*., 2018;
Burton *et al*., 2012;
Schneider *et al*., 2015;
Slovak *et al*., 2015;
Tudor *et al*., 2020;
Zecca *et al*., 2016).

Randomised controlled trials are required to provide a robust evidence-base for using TTNS for neurogenic bladder storage related symptoms in MS. Therefore, there is a need to assess the feasibility of TTNS in storage symptoms among people with MS using, widely available and affordable device, the transcutaneous electrical nerve stimulation (TENS) unit to proceed with a definitive randomised trial.

### Specific objectives

The overreaching aim of this study is to assess whether transcutaneous tibial nerve stimulation (TTNS) is feasible as a treatment for bladder storage symptoms in people with MS. In particular, the study will explore the feasibility and acceptability of TTNS application in people with MS by addressing the following specific objectives:

*The primary objectives are* to a) assess the recruitment and retention rates, b) investigate the completion rate and appropriateness of outcome measures by participants; c) assess safety by reporting the number of participants with adverse events; d) determine participants’ adherence to the treatment protocol, and e) assess participant’s satisfaction with TTNS application.

*The secondary objectives are to* a) evaluate the preliminary effectiveness of TTNS in managing bladder storage symptoms in MS; and to b) determine the effect of TTNS on quality of life in people with MS.

Addressing these objectives will establish a foundation for future definitive randomised trial to explore the efficacy of TTNS on bladder storage symptoms in MS.

## Methods

The CONSORT extension for pilot and feasibility studies will be followed to standardise the conduct and reporting of the study (
Eldridge *et al*., 2016). Ethical approval was obtained from the Faculty of Education and Health Sciences Research Ethics Committee at the University of Limerick [2020_06_07_EHS]. This study was registered with ClinicalTrials.gov on 27
^th^ August 2020 (
NCT04528784). The trial registration platform will be updated if any changes are made to the trial.

### Study design

A single-arm experimental study to assess the feasibility of TTNS in MS bladder storage symptoms.

### Setting

The intervention will be accessible to community dwelling people with MS in Ireland and self-administered by participants in their own homes.

### Participants

Inclusion criteria: People with a self-reported diagnosis with any type of MS who are ambulatory; aged ≥18 years old; who have at least one bladder storage related symptom such as urinary frequency, urinary urgency, nocturia, with or without incontinence; and who are willing to give written informed consent.

People with MS will be excluded if they have: indwelling urethral catheter; indwelling suprapubic catheter; urologic disease including bladder malignancy; diabetic mellitus; pregnant women or plan to be pregnant during the study time; recent pelvic related surgery <1 year; pacemaker or other metallic internal devices; urinary tract infections (UTIs) during recruitment phase.

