### Statistical methods

SPSS software (Version 26.0. Armonk, NY: IBM Corp) will be used for statistical analysis:

•
*The primary outcomes* will be analysed using descriptive statistics (numbers, means, and percentage) with 95% confidence interval (CI). Medians and interquartile ranges will be reported where data are not normally distributed.

•
*The secondary outcomes* for the scores of ICIQ-OAB and King’s Health questionnaire at the baseline, and at the end of week 6 will be reported as mean scores with SD and changes in scores between baseline, and week 6 will be examined using T-tests to provide a quantitative indicator of the significance of the changes in the assessment measures following stimulation sessions. The non-parametric equivalent tests will be employed where data are non-parametric.

The incidence of nocturia, incontinence and urinary frequency and urgency will be reported across the two groups and differences will be quantified using a Chi-squared test.

The scale of Patient Perception of Intensity of Urgency Scale (PPIUS) will be assessed using descriptive statistics means and standard deviation (SD).

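### Neither the entry criteria nor the weekly calls address recent bladder-treatment change or MS relapse, so either may be counted as change after TTNS in the secondary outcomes

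*Protocol article*

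**What the plan says.** Under Participants, the article admits "People with a self-reported diagnosis with any type of MS who are ambulatory; aged ≥18 years old" and "who have at least one bladder storage related symptom such as urinary frequency, urinary urgency, nocturia, with or without incontinence". The exclusions close with "recent pelvic related surgery <1 year; pacemaker or other metallic internal devices; urinary tract infections (UTIs) during recruitment phase". The only items tied to time are pelvic surgery, pregnancy and urinary tract infection. No item concerns recent or changing bladder treatment, and none concerns MS relapse.

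The Background describes other treatments that act on the same symptoms. It says that "anticholinergic medication are considered a first-line treatment for neurogenic bladder population", with short-term efficacy but limited long-term tolerance. It also describes pelvic floor muscle training as effective, and it ranks botulinum toxin injection as the most effective option while listing "the need for repeated injections" among its limitations.

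Study design: "A single-arm experimental study to assess the feasibility of TTNS in MS bladder storage symptoms". Under Participant identification and consent, the symptom and quality-of-life measures are completed once at week 0 and once at the end of week 6. The weekly calls cover adherence, adverse events and whatever the participant brings up.

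A secondary objective is to "evaluate the preliminary effectiveness of TTNS in managing bladder storage symptoms in MS". The Statistical methods section applies t-tests to the change in ICIQ-OAB and King's Health Questionnaire scores "to provide a quantitative indicator of the significance of the changes in the assessment measures following stimulation sessions".

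**The concern.** The secondary objectives rest on each person's own change over six weeks. Without a concurrent control arm, nothing balances out other causes of change. With a single baseline, nothing shows whether a participant was already improving or worsening at entry.

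The article's own Background makes such causes foreseeable: a drug with short-term effect and poor long-term tolerance will be started and stopped, and an injection that must be repeated wears off. As the criteria stand, someone who has just begun a bladder drug, someone whose injection is wearing off and someone recovering from a relapse can all enter. Their week 0 to 6 change then goes into the same t-test as everyone else's. A new treatment or a recovery would flatter TTNS; wearing-off or a new relapse would count against it. The article intends the results to lay the ground for a definitive randomised trial, so a distorted preliminary estimate would be carried forward.

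**Working it through.** **1. Does any part of the article supply the missing condition?**

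| Place in the article | What it provides | Deals with treatment change or relapse? |
|---|---|---|
| Participants, inclusion | MS type, age, ambulatory, at least one storage symptom, consent | No |
| Participants, exclusion | Catheters, urological disease, diabetes, pregnancy, pelvic surgery, metallic devices, infection | No; the device item probably removes implanted stimulators only |
| Participant identification and consent, assessments | One baseline, one week-6 assessment | No run-in or repeated baseline |
| Same section, diaries | Adverse events and adherence; observations about applying the stimulation | Not a stated item |
| Same section, weekly calls | Adherence, adverse events, issues raised; responses documented | Only if the participant raises it |
| Statistical methods | t-tests of change, or non-parametric equivalents | No adjustment or sensitivity summary stated |
| Extended data | Screening form and demographic sheet listed, contents not shown | Unknown at baseline |

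So no entry condition and no planned follow-up question is stated. Baseline recording on the forms that are not shown remains possible.

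**2. Shift in the mean change.** The article gives no SD, effect size or power for these outcomes, so there is no figure to reproduce. Inputs: n = 20 (Sample size); ICIQ-OAB range 0 to 16 (Outcomes); a shift of 3 points per affected person (assumed).

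Shift in mean = k × 3 / 20 = 0.15k, where k is the number affected in the same direction.

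- k = 2: 2 × 3 / 20 = 0.30 points
- k = 5: 5 × 3 / 20 = 0.75 points

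With effects in both directions only the net number counts: three people improving and two worsening give (3 − 2) × 3 / 20 = 0.15 points.

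**3. Effect on the t-test.** Assumptions, none from the documents: paired t-test, two-sided 5% level, no TTNS effect, SD of change 2.5 to 3.5, shift of 2 to 4 points, all affected people improving. There were 100,000 simulations per scenario. The nominal chance of a significant improvement is 2.5%.

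| Affected of 20 | Spurious mean improvement | Chance of a significant improvement |
|---|---|---|
| 2 | 0.2 to 0.4 | 4% to 7% |
| 4 | 0.4 to 0.8 | 6% to 17% |
| 6 | 0.6 to 1.2 | 10% to 34% |
| 8 | 0.8 to 1.6 | 14% to 58% |

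The same mean shifts in the other direction could hide a benefit. For scale, at n = 20 the test reaches significance at an observed standardised change of 0.47 and has 80% power at a true one of 0.66.

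**The case against.** The case on the other side has several parts, and some of it stands.

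- **The forms are not shown.** The screening form, the demographic sheet and the eligibility call may already ask about drugs, injections or relapse. This stands: a reader might infer that the study cannot identify the people concerned, and the article does not support that. Recording at baseline is still not an entry criterion, and it would not catch changes during weeks 0 to 6. The weekly calls could bring such a change to light, but only by chance.
- **Only secondary, preliminary objectives are touched.** This also stands. The five primary objectives concern recruitment and retention, outcome completion, safety, adherence and satisfaction. A reader might infer that earlier users of tibial stimulation would raise adherence and satisfaction. Nothing in the article supports this, and earlier users who did not benefit could lower both.
- **The size is assumed.** True. The article gives no rate of recent treatment change or relapse, and opposite effects may cancel.
- **A single-arm change cannot be attributed to TTNS anyway.** Correct: regression to the mean and placebo response remain. But the article chooses to significance-test the change, and this source of distortion, unlike those, can be recorded at almost no cost.
- **Broad entry suits a feasibility study.** This is a fair argument against relying on a stricter criterion alone. It is no argument against asking and reporting.

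**Conclusion.** The point holds in limited form. As written, the plan neither requires stable bladder treatment and MS at entry nor states a check for change during follow-up. Such changes may therefore be mixed into the week 0 to 6 symptom and quality-of-life results, in either direction.

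It would go too far to say that they will be mixed in: that depends on who enrols and whether the change comes to light, and the article gives no figure for either. The 0.15 points per affected participant rests on the assumed 3-point shift and on all effects running the same way. The simulated error rates rest further on an assumed SD. These figures show how the distortion scales; they do not estimate its size in this study. The consequence is confined to the secondary outcomes. It merits correction because the remedy is cheap and changes not recorded at the time are hard to recover later.

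**What to change.** 1. At the eligibility call, ask about current and recent bladder treatment (drugs, botulinum toxin, pelvic floor training, nerve stimulation) and about MS relapse, unless the screening form already does so.
2. Add one question to each weekly call: has any bladder treatment changed, or has a relapse occurred, since the last call?
3. Report the week 0 to 6 changes for all participants and again without those who had such a change or relapse. Present the second result as a sensitivity summary, not a replacement, because a change of treatment during follow-up may itself depend on how symptoms are responding.
4. Preferably, add to the Participants section a criterion of unchanged bladder treatment and no relapse over a look-back period that the investigators fix before first enrolment, with re-screening allowed. Count people deferred for this reason in the recruitment outcome, so that the feasibility result stays interpretable.

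No length of period is proposed here, and no one's care is altered. Items 1 to 3 cost a few screening questions, one weekly question and one extra summary. Item 4 costs one eligibility line and may slow recruitment slightly against the expected 20 people in two months. If that is unacceptable, items 1 to 3 alone meet most of the concern.
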